#### Logbook

The PAs will be asked to complete a logbook entry after each meeting with a patient to document the duration of the meeting, topics discussed, difficulties experienced, perceived added value for the patient, and anything else they deem relevant. This logbook will be developed for this study (Additional file 6: questions 3 to 42).

#### Health and social care provider questionnaires

To better identify the organizational factors that can influence the integration of PAs in clinical oncology teams, we will administer validated questionnaires to health and social care provider participants at the beginning and end of the study to assess the evolution of their collaborative practices [50] (Additional file 7: questions 22 to 47), their capacity to make changes to their collaborative practice [51, 56, 57] (Additional file 7: questions 48 to 54), their perception about their relations with the patients and the PA’s [50] (Additional file 7: questions 64 to 74) and with a questionnaire that will be developed for this study about their openness to integrating PAs in their team and potential barriers to this integration (Additional file 7: questions 56 to 62 and 75). Sociodemographic data will be collected also **(**Additional file 7: questions 80 to 97)**.** Considering a minimum response rate of 35%, to obtain a sample size of 15 health and social care providers from each site, 43 will be invited, from each setting (*n* = 258 (6X43)), to respond to the questionnaires.

### Quantitative analyses

Statistical analyses will be performed using IBM SPSS Statistics version 25 [58] and SAS 9.4 [59]. Results with *p* < 0.05 will be considered significant. Descriptive statistics will be used to summarize each setting’s patients’ and PAs’ socio-demographic and clinical variables and the health and social care providers’ professional experience. Student t tests or non-parametric tests, such as the Mann-Whitney test, will be used for continuous variables. At the organizational level, the challenges encountered throughout the implementation of the PA program and the engagement and satisfaction of the health and social care oncology teams will be examined. At the clinical level, the effects on the patients, the PAs and the health and social care oncology teams will be assessed.

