## Methods/design

### Study design

The planned approach is a longitudinal multiple in-depth case study with two levels of analysis (clinical and organizational) that will be conducted over 4 years at six different sites. The longitudinal design is necessary to account for inevitable delays over the course of the implementation, to allow the time to consolidate changes made at each case site, and to allow the time needed to avoid making premature conclusions regarding the impacts of the changes [38, 39]. The multiple case study design allows for the in-depth analysis of the implementation processes in diverse oncology contexts. Qualitative and quantitative data will be used to document the intervention for each case, to examine the implementation processes, in their respective contexts, and to report their respective effects at the clinical and organizational levels [40]. This design is consistent with realistic evaluation [30] and intervention action-research [29] and structures our in-depth investigation of the links between the implementation and co-construction mechanisms and our ability to capture the challenges and the effects of the intervention.

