### Governance

Each site will assemble a local project committee made up of PAs, oncologists, administrators, nurses, oncology nurse coordinators, allied health professionals (e.g., social worker or psychologist), and a research assistant. An overarching study committee comprising the research coordinator for all sites, the research assistants of each site, and an administrator/clinician representative from each site will be in charge of setting up the PA program, discussing challenges and finding solutions, and facilitating the assessment. A community of practice of approximately 30 PAs (between 3 to 5 PAs will be recruited per site) will be formed so the PAs can share successes and challenges and learn from one another. Finally, a steering committee made up of the decision makers and researchers will meet annually to discuss the progress of the project, provide advice on how to carry out the research and comment on the results, and an advisory committee made up of the site representatives (the research assistant and the administrator or clinician) and researchers will review and interpret results of each phase of the study.

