### Participants

For each setting, the representatives of high/mid-level managers working in the targeted program, the health and social care professional (HSP) team members, the patients, and the PAs (to be recruited) will be invited to participate in the project. For the patients, the inclusion criteria will be understanding written and spoken French, undergoing cancer screening or treatment, being at least 18 years old and have had at least one meeting with a patient advisor. All participants meeting the inclusion criteria will be invited to participate. This is therefore a consecutive sampling. Professionals and patient advisors will be approached by email. Patients will be approached by telephone or face-to-face through the patient advisor at their initial meeting. All participants will sign an informed consent form approved by Centre Hospitalier de l’Université de Montréal’s research ethics committee. Indeed, this study was submitted to and approved by the Centre Hospitalier de l’Université de Montréal’s research ethics committee.

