#### Questionnaires for patients

Measurements will be taken before the meeting with the PA (T0), immediately following this meeting (T1), and again 1 month after this meeting (T2). Two of the questionnaires used will be co-constructed with patients specifically for this study and assess: patients’ care experience (Additional file 4, questions 41 to 67) and patients’ experience with PAs (Additional file 4: questions 69 to 100 and 102 to 127), following the procedures and sequence of content validation outlined by Haynes and colleagues (1995) [53]. Three validated questionnaires will be used to assess patients’ psychological distress (K6) [49] (Additional file 4: questions 141 to 146), treatment adherence [47] (Additional file 4: questions 148 to 159), and ability to cope with cancer (CASE) [48] (Additional file 4: questions 129 to 140). Data variables of patients’ sociodemographic and clinical characteristics will be collected including sex, age, and type of cancer (Additional file 4, questions 22 to 39). To obtain a complete data set for 30 to 50 patients per site and based on a previously established response rate of 70% [54, 55], we will plan to recruit at least 40 to 70 patients from each site.

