## Discussion

Research on peer support in oncology has shown promising results [6–13], particularly for helping people navigate the healthcare system. However, studies where patients who have experienced cancer care are integrated in the clinical teams are rare. This study will be the first to integrate PAs as full-fledged members of the clinical oncology team and to assess the potential effects at the clinical and organizational levels [64]. The only study we are aware of is currently underway in two regions in France and is exploring the effect of integrating “peers” who have experienced disease in clinical teams to support patients on communication and engagement in their care. Initial results indicate that recruiting peers and keeping them engaged in this role is difficult. However, unlike the study we will conduct, the peers are not full-fledged members of the clinical teams. Also, given that PAs will be integral members of the health and social care oncology team, our study will likely suggest means to successfully integrate care partnerships and services into clinical oncology teams. The originality of the PA’s role in our study will complement the body of research on peer support and patient navigators. Finally, given the mixed methods nature of our study, it will be possible to study variability between settings, and thus, delineate various situations that can be encountered and reinforce the external validity of our study.

Understanding the integration of patients into health and social care oncology care teams requires an analysis of the ethical and legal issues at play. For the most part, in this study, the potential issues are for PAs to access patient health records, the management of inform consent, the respect of confidentiality, the responsibility of the study settings towards the PAs and the patients, and the recognition and financial compensation of the PA’s as work [65]. These issues must be considered in conjunction with the role of the healthcare professionals and their relationships with the PA. Identifying the risks for the PAs, particularly psychological and social ones, as well as the implementation of terms and conditions to manage these risks are also part of the ethical challenges to document.

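### The named tests (Student t, Mann-Whitney) do not fit the effects to be assessed, which are changes over time in one group of clustered patients

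*Protocol article*

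**What the plan says.** In the protocol article, Quantitative analyses fixes the criterion ("Results with *p* < 0.05 will be considered significant") and names the inferential methods once: "Student t tests or non-parametric tests, such as the Mann-Whitney test, will be used for continuous variables". It then promises that "At the clinical level, the effects on the patients, the PAs and the health and social care oncology teams will be assessed", without giving a method for that step. No paired test, repeated-measures model or adjustment for PA or site appears.

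The design is described elsewhere in the article:

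- **Patients, timing**: the section Questionnaires for patients sets three occasions: "Measurements will be taken before the meeting with the PA (T0), immediately following this meeting (T1), and again 1 month after this meeting (T2"). Table 1 lists the K6, CASE and treatment adherence scales at all three times.
- **Patients, eligibility** (Participants): each must "have had at least one meeting with a patient advisor".
- **PAs and providers** (Table 1): the K6 for PAs, and the provider scales on collaboration, innovation and partnership, are collected at T0 and T2.
- **Structure**: a study "that will be conducted over 4 years at six different sites" (Study design), where "between 3 to 5 PAs will be recruited per site" (Governance).
- **Between-site aim** (Discussion): "it will be possible to study variability between settings".

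**The concern.** Every enrolled patient has met a PA, so there is no untreated group to compare with. An effect on patients can only be a change within patients; for PAs, and for providers where responses can be linked, it is a change from T0 to T2. The one non-parametric test named is for two independent groups. Student t could be meant as paired or unpaired, and the text does not say which.

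The two readings fail in opposite directions. Unpaired tests discard the within-person correlation and become too conservative, so a real change may be missed. Paired tests that ignore shared PAs become too liberal if patients of the same PA tend to change alike, so a chance change may be declared. Neither reading handles three occasions together or compares six sites.

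Assessing effects is the third stated objective, and the results are to inform a later randomized trial. A missed or spurious signal would carry into that decision.

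**Working it through.** **The article's own figures.** It gives no effect size, SD, power, within-patient correlation or intraclass correlation (ICC), so there is no power figure to reproduce. Its only sample-size arithmetic is inflation for response. For providers, 15/0.35 = 42.9, so 43, and 6 × 43 = 258, as stated. For patients, 30/0.70 = 42.9 and 50/0.70 = 71.4, against the stated 40 and 70. That difference is a separate matter. The inputs used here are 30 to 50 complete patients per site, 3 to 5 PAs per site and six sites. The correlation r, the ICC and the effect size are assumptions, shown as ranges. Tests are taken as two-sided.

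**Step 1. Match of test to comparison.**

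| Comparison | Independent-samples t or Mann-Whitney | Paired t |
|---|---|---|
| Patients, T0 vs T2 | wrong structure | pairing handled, clustering not |
| Patients, T0/T1/T2 jointly | no | no |
| PAs, T0 vs T2 | wrong structure | suitable |
| Providers, T0 vs T2 | wrong structure if responses are linked | pairing handled if linked, site not |
| Six sites | two groups at a time only | no |

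**Step 2. Independent-samples reading.** With n patients and equal variances, the test assumes variance 2σ²/n for the mean change. The true value is 2σ²(1−r)/n. The SE is therefore overstated by 1/√(1−r), and the actual size is 2[1−Φ(1.96/√(1−r))].

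- r = 0.5: SE ratio 1.41, actual size 0.0056
- r = 0.7: SE ratio 1.83, actual size 0.0003

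Power for an assumed change of 0.2 SD at r = 0.5, all sites pooled and without clustering:

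- 180 patients (6 × 30): 0.465 unpaired, 0.765 paired
- 300 patients (6 × 50): 0.756 unpaired, 0.934 paired

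**Step 3. Paired reading, clustering ignored.** If each patient is attached to one PA, the number per PA runs from 30/5 = 6 to 50/3 = 16.7. The design effect is 1 + (m−1) × ICC, where the ICC is that of the change scores, and the actual size is 2[1−Φ(1.96/√DEFF)].

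| Patients per PA | ICC 0.01 | ICC 0.05 | ICC 0.10 |
|---|---|---|---|
| 6 | DEFF 1.05, size 0.056 | 1.25, 0.080 | 1.50, 0.110 |
| 10 | 1.09, 0.060 | 1.45, 0.104 | 1.90, 0.155 |
| 16.7 | 1.16, 0.068 | 1.79, 0.142 | 2.57, 0.221 |

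**Step 4. Simulation check** (24 PAs × 10 patients, no true mean change, 4,000 runs). Entries are rejection rates at nominal 0.05.

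| r | ICC | Unpaired t | Mann-Whitney | Paired t | t on PA-mean changes |
|---|---|---|---|---|---|
| 0.5 | 0 | 0.0065 | 0.008 | 0.049 | 0.050 |
| 0.7 | 0 | 0.0005 | 0.0005 | 0.046 | 0.048 |
| 0.5 | 0.05 | 0.0215 | 0.0215 | 0.098 | 0.054 |
| 0.7 | 0.05 | 0.003 | 0.0035 | 0.102 | 0.049 |
| 0.5 | 0.10 | 0.0485 | 0.048 | 0.165 | 0.052 |
| 0.7 | 0.10 | 0.007 | 0.009 | 0.155 | 0.047 |

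The simulation agrees with the formulas. At r = 0.5 and ICC 0.10 the two errors happen to cancel, but nothing in the plan secures that. Only the analysis that respects both pairing and PA stays near 5% throughout.

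**Step 5. What a remedy must do.** A random PA intercept adds the same amount at T0 and T2 for each patient of that PA, so it cancels from the change. With complete T0/T2 pairs the SE of the time effect returns essentially to that of the paired t, whose error is about 10% at ICC 0.05 and 10 patients per PA. T0 precedes the PA meeting, so any PA influence lies in the change, and the clustering term must act there.

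**The case against.** The best defence is that the sentence is loose rather than wrong. Mann-Whitney is offered only as an example, and Student t tests include the paired form. The sentence follows the descriptive summary of each setting, and the later sentence on effects names no method. Two-group comparisons are possible, such as the three university hospital centres against the three regional authorities (Settings). A fuller protocol or analysis plan may name a suitable model. All of this is fair, and it means the article does not expressly assign Mann-Whitney to change over time. It does not remove the point. These are the only tests the article names for effects judged at p < 0.05, and the one non-parametric example has the wrong structure for T0 against T2. That is a stated method, not missing detail.

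Several stronger readings are tempting but unsupported:

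- *Each patient is nested in one PA.* The article requires at least one meeting with a PA and does not say that a patient sees only one. Nesting in sites is clear; nesting in PAs is probable.
- *Provider data are paired.* Nothing says that responses at the beginning and end of the study are linked to the same individuals.
- *About 30% of patients drop out by T2.* The 70% is a response rate. The article does not say whether the loss is at entry or at follow-up, so no claim about T2 dropout bias rests on it.
- *There is a comparison group after all.* Table 1 mentions expectations of patients without PA accompaniment, but the eligibility rule leaves no such group among enrolled patients.

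**Conclusion.** The point holds as a should-fix. Taken as independent-samples tests on T0 against T2, the named methods overstate the SE by 1.41 to 1.83 (assumed r 0.5 to 0.7), run at about 0.6% to 0.03% instead of 5%, and lose power. Taken as paired t tests, they handle two occasions only and ignore clustering. The true error is then about 6% to 22% for an assumed ICC of change of 0.01 to 0.10, with each patient attached to one PA.

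A reader might infer that the reported p-values must be wrong or cannot be interpreted. The documents do not support that: with paired tests and an ICC of change near zero, they would be about nominal. Nor is this a confirmatory failure. The study assesses feasibility and explores effects, and the article names no primary endpoint. The point still matters because significance is fixed at 0.05 and the results feed the design of a randomized trial.

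**What to change.** State in Quantitative analyses that Mann-Whitney and unpaired t tests are not used for change over time. Then name the methods by group:

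- **Patient scales:** a linear mixed model with time (T0, T1, T2), site and site-by-time as fixed effects and a random patient effect, using all available observations. The site-by-time term serves the stated interest in variability between settings.
- **PA clustering:** let it act on change through a random PA-by-time effect (or PA random slope), or use cluster-robust SEs by PA with a small-sample correction, since there are only 18 to 30 PAs (6 × 3 to 6 × 5). A PA random intercept alone is not enough. PA identity can come from the logbook, which records PA and patient for each meeting. The text should say how patients who met more than one PA are assigned.
- **PAs:** paired t or Wilcoxon signed-rank test on T0 and T2.
- **Providers:** where T0 and T2 responses can be linked, a mixed model with a random person effect and site in the model; otherwise a comparison that accounts for site.

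The mixed model does not repair loss that depends on unobserved T2 values, and the text should not claim that it does.

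The cost is a change of wording, slightly more analysis work and possibly wider intervals. SAS 9.4 is already planned and no new data collection is needed for patients or PAs. Linking provider responses would need an identifier if none is kept.

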### Integrated knowledge translation

Our action research intervention will be conducted in close collaboration with the actors on the ground and is inspired by realistic evaluation methodology [30, 32]. The study will be conducted simultaneously with the co-construction of the intervention to enable knowledge and expertise sharing between the producers and the users of the results [27]. This strategy accelerates the adoption of new practices based on research results, for complex and innovative interventions [60, 61].

The study results will be shared with those participating in the implementation and assessment of the PA intervention according to the components of the Knowledge to Action framework [62]. This allows for recursive actions that will make it possible to write summaries together with each administrator/clinician representative and PAs on a site-by-site basis, offer exchange areas between researchers, health and social care teams and PAs, and implement results to improve health and social care service offerings and the health and social care system as a whole [63]. To this end, throughout the study we will regularly share the preliminary results with corresponding site. Also, over the 4 years of this study, we will hold annual events assembling researchers, decisionmakers, patients, PAs, health and social care oncology teams, and administrators to discuss the results and co-construct best practices based on them. In addition, our multidisciplinary research team includes stakeholders with expertise as: patients, family doctors, medical specialists, human factors, change management, administration, ethics, law, integrated knowledge translation, mixed methods.

### Deliverables

A toolbox (English and French) including the tools developed by the site stakeholders and the research team members to address the needs that emerge over the course of the co-construction and implementation phases of the study will be made available for all health and social care organizations. It will include: 1) educational material for the PA training dealing with subjects covered by the PA during their meetings with patients and the ethical and legal issues that are identified in the study; 2) implementation materials such as an assessment of the facilitating factors, PA recruitment process, confidentiality agreement forms for the PAs, PAs casefile notes templates that, once completed, are integrated into the accompanied patients’ health records, contracts regarding rights and responsibilities of the PAs and the study sites, a legal framework for the implementation of PA programs; 3) PA program promotion materials; 4) assessment tools, including questionnaires and their associated documentation, and informed consent forms. This toolbox will be freely available on the website of the research Chair for research and evaluation of leading edge technologies and practices – citizen and patient engagement in health system and organization transformation (https://chaireengagementpatient.openum.ca/), the website of the Centre for excellence in partnerships with patients and the public (https://ceppp.ca/en/), and the websites of the participating settings.

## Discussion

Research on peer support in oncology has shown promising results [6–13], particularly for helping people navigate the healthcare system. However, studies where patients who have experienced cancer care are integrated in the clinical teams are rare. This study will be the first to integrate PAs as full-fledged members of the clinical oncology team and to assess the potential effects at the clinical and organizational levels [64]. The only study we are aware of is currently underway in two regions in France and is exploring the effect of integrating “peers” who have experienced disease in clinical teams to support patients on communication and engagement in their care. Initial results indicate that recruiting peers and keeping them engaged in this role is difficult. However, unlike the study we will conduct, the peers are not full-fledged members of the clinical teams. Also, given that PAs will be integral members of the health and social care oncology team, our study will likely suggest means to successfully integrate care partnerships and services into clinical oncology teams. The originality of the PA’s role in our study will complement the body of research on peer support and patient navigators. Finally, given the mixed methods nature of our study, it will be possible to study variability between settings, and thus, delineate various situations that can be encountered and reinforce the external validity of our study.

Understanding the integration of patients into health and social care oncology care teams requires an analysis of the ethical and legal issues at play. For the most part, in this study, the potential issues are for PAs to access patient health records, the management of inform consent, the respect of confidentiality, the responsibility of the study settings towards the PAs and the patients, and the recognition and financial compensation of the PA’s as work [65]. These issues must be considered in conjunction with the role of the healthcare professionals and their relationships with the PA. Identifying the risks for the PAs, particularly psychological and social ones, as well as the implementation of terms and conditions to manage these risks are also part of the ethical challenges to document.

This study, funded in part by the Canadian Institutes of Health Research, will help to promote the care partnership approach at the clinical level and to develop the knowledge on this subject. It will also contribute to the knowledge regarding ethical and legal issues of developing care partnership for health and social care organizations interested in integrating PAs on clinical care teams.

